### Sample size estimation

According to previous literature,^5 8^ the incidence of PIH was approximately 35% for patients undergoing elective non-cardiac surgery. Considering a required number of 10 events per variable,^31–33^ we plan to recruit 657 patients for model development and internal validation (657=23×10/0.35). Another 281 patients will be included continuously for model temporal validation. Therefore, the planned sample size will be set to 938 patients.

### Missing data

We will use multiple imputations when a variable has ≤5% missing data, while variables with >5% missing data will be excluded from the analysis.

### Statistical analysis

#### Descriptive analysis and comparisons

Continuous variables will be presented as mean±SD and analysed using the Student’s t-test when data are normally distributed, or presented as medians with IQRs and analysed using the Mann-Whitney U test when data are not normally distributed. Categorical and ordinal data will be presented as number (%) and analysed using the χ^2^ or Fisher’s exact tests. The absolute standardised difference (ASD) will be used to compare the baseline data between the development and validation cohort, with ASD >0.14 (ie, $1.96\times \sqrt{\left(657+281\right)/\left(657\times 281\right)}$) indicating imbalance.

#### Development of the prediction model

The development cohort (n=657) will be used to construct the model. We will use the least absolute shrinkage and selection operator (LASSO) regression analysis for variable shrinkage and selection in the development of linear regression model. For centralisation and normalisation of variables, we will use the 10-fold cross-validation in the LASSO regression analysis, which will be repeated 10 times. In the 10 times 10-fold cross-validation, we will divide the development cohort into 10 equal parts. Then 9/10th of the data will be used to retrain the model and the remaining 1/10th will be used for validating the statistical accuracy in each time. The best lambda value will be selected. Based on the optimal predictors derived from the LASSO analysis, we will use the multivariable logistic regression analysis to develop a prediction model.

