**Methods and analysis:**

A total of 938 elderly surgical patients (n=657 for development and internal validation, n=281 for temporal validation) will be continuously recruited at The First Affiliated Hospital of Soochow University in Suzhou, China. The main outcome is PIH during the first 15 min after anaesthesia induction or before skin incision (whichever occurs first). We select candidate predictors based on published literature, professional knowledge and clinical expertise. For model development, we will use the least absolute shrinkage and selection operator regression analysis and multivariable logistic regression. For internal validation, we will apply the bootstrapping technique. After model development and internal validation, temporal validation will be conducted in patients recruited in another time period. We will use the discrimination, calibration and max-rescaled Brier score in the temporal validation cohort. Furthermore, the clinical utility of the prediction model will be assessed using the decision curve analysis, and the results will be presented in a nomogram and a web-based risk calculator.

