### Study outcome

The study outcome is PIH during the first 15 min after anaesthesia induction or before skin incision (whichever occurs first). Preoperative baseline blood pressure will be recorded when patients are comfortably seated in the ward. During anaesthesia induction, patients will be monitored using non-invasive cuff blood pressure at 1 min interval. Hypotension is defined as either a 30% reduction in mean arterial pressure (MAP) from baseline or absolute MAP ≤65 mm Hg. Dual definitions for diagnosis of hypotension (either a relative reduction in MAP or an absolute threshold of MAP) have been used in many recent studies.^20–25^

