**Figure 1 F1:**
[figure not shown]
Study flowchart.

Candidate predictors are selected based on published data,^14^ professional knowledge and clinical expertise. The following clinical variables will be recorded in the case report forms (online supplemental file 2). The research assistant will fill out the preoperative potential predictors section of the form during the preoperative visit, and document variables in the intraoperative potential predictors section and values of heart rate (HR) and non-invasive cuff blood pressure (NIBP) in the outcome section during the case when looking at the monitor.

10.1136/bmjopen-2023-074181.supp2Supplementary data

During the analysis phase, we will calculate MAP at each time point using the traditional formula (MAP=diastolic blood pressure+0.33×pulse pressure), and we will calculate the relative threshold (30% MAP reduction from baseline). Based on these, we can determine the occurrence of PIH.

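### LASSO selection is written for a linear regression model although PIH is binary and the final model is logistic, and cross-validation is given the task of centring and normalising the variables

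*Protocol article*

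**What the plan says.** Under Study outcome the endpoint is a threshold event: "Hypotension is defined as either a 30% reduction in mean arterial pressure (MAP) from baseline or absolute MAP ≤65 mm Hg". Under Data collection, MAP at each time point and the relative threshold are calculated at the analysis stage, and then "Based on these, we can determine the occurrence of PIH". The analysed outcome is therefore whether PIH occurred, not a blood pressure value.

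Under Development of the prediction model, LASSO is used "for variable shrinkage and selection in the development of linear regression model". The next sentence reads "For centralisation and normalisation of variables, we will use the 10-fold cross-validation in the LASSO regression analysis", repeated 10 times. Nine tenths of the data retrain the model and "the remaining 1/10th will be used for validating the statistical accuracy in each time". Then "The best lambda value will be selected". With the predictors that LASSO retains, "we will use the multivariable logistic regression analysis to develop a prediction model".

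The abstract (Methods and analysis) says only that "we will use the least absolute shrinkage and selection operator regression analysis and multivariable logistic regression". The Discussion mentions the repeated 10-fold cross-validation and the best lambda again. Neither place gives a model family or a loss for the LASSO step.

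**The concern.** Two statements in the operative methods text are wrong on their face.

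- **Model family.** One paragraph names a linear model for selection and a logistic model for the final fit, with the same binary outcome. An analyst who follows the text would select predictors under a linear-probability model and then fit a different model.
- **Role of cross-validation.** Cross-validation tunes lambda. Centring and scaling are separate preprocessing. The LASSO penalty depends on units, and the candidates include pressures, heart rates, a fluid volume, a fasting duration, drug doses, scale scores and yes/no comorbidities. The article intends standardisation but attaches it to a procedure that cannot perform it.

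At stake is which of the 23 candidates reach the nomogram and the web calculator. Two competent analysts could build different models from this paragraph.

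**Working it through.** **1. The plan's own figures.** Candidates: 15 preoperative + 8 intraoperative = 23. Sample size estimation gives 23 × 10 / 0.35 = 657.14, which reproduces the stated 657. Expected events are 657 × 0.35 ≈ 230. Neither figure depends on the LASSO family, so no stated number changes with the fix.

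**2. The statements side by side.**

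| Element | What the article implies |
|---|---|
| Outcome (Study outcome; Data collection) | Binary |
| LASSO step (Development) | Linear regression model |
| Final model (Development; abstract) | Logistic regression |
| Purpose given for cross-validation | Centring and normalising |
| What the described cross-validation does | Train on 9/10, test on 1/10, choose lambda |
| Criterion for lambda | Not named beyond accuracy and best value |

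Rows 1 and 3 agree with each other and conflict with row 2. Rows 4 and 5 conflict within one paragraph.

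**3. What the literal reading would do.** A linear LASSO minimises the mean of (y − a − xβ)² plus λΣ|βⱼ|, up to a constant scaling of the first term. A logistic LASSO minimises binomial deviance plus the same penalty. With y equal to 0 or 1, squared error is the Brier score, which is a proper score. What differs is the working model: additive on the risk scale in one case, additive on the log-odds scale in the other.

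**4. Why standardisation needs its own statement.** If a predictor is re-expressed in units c times smaller, its coefficient falls to 1/c of its value, and so does its contribution to the penalty. As an example, a coefficient per minute of fasting is 1/60 of the coefficient per hour. Without scaling, the unit of recording would influence selection.

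**5. Size, by simulation.** All runs used n = 657, 23 candidates and about 35% incidence. Effect sizes are assumptions, because the article gives none.

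| Assumed setting | Datasets | Linear and logistic sets differ | Logistic LASSO differs from itself when folds are reshuffled |
|---|---|---|---|
| True AUC 0.70, identical folds | 60 | 43% (mean 0.53 predictors) | not run |
| Coefficients 1.8 times as large, identical folds | 60 | 70% (mean 1.3 predictors) | not run |
| Eight true effects of 0.2 to 0.6 per SD, one 10-fold run | 60 | 39/60 = 65% | not run |
| True AUC 0.70, one 10-fold run | 60 | 35% | 47% |
| True AUC 0.80, one 10-fold run | 60 | 80% | 53% |
| True AUC 0.70, three repeats | 40 | 18% | 28% |
| True AUC 0.80, three repeats | 40 | 70% | 33% |

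In the third row, mean set sizes were 14.45 and 14.35, and mean Jaccard overlap was 0.926 (minimum 0.73). The implied union is about (14.45 + 14.35) / 1.926 ≈ 14.95 predictors, so the sets differ by about 0.074 × 14.95 ≈ 1.1 predictors.

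In the last four rows the selected predictors were refitted by logistic regression, as the plan does, and tested on 50,000 simulated patients. The mean absolute difference in AUC was 0.0002 to 0.0005, at most 0.005 in any dataset, with no consistent direction.

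**6. Precision.** With 60 datasets, 43% carries a 95% interval of 0.43 ± 1.96 × √(0.43 × 0.57 / 60) = 0.43 ± 0.13, or roughly 30% to 56%. None of these runs used the planned 10 repeats.

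**The case against.** The strongest defence is that the word linear is a slip. The paragraph ends in logistic regression, the abstract pairs LASSO with logistic regression, and events-per-variable sizing, the Hosmer-Lemeshow test and the area under the ROC curve all presuppose a binary outcome. That is plausible. It does not remove the error, because linear is the only family written down for the selection step.

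A reader might go further than the text allows in three ways.

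- **That the penalty is tuned on a wrong loss.** The article names no loss. The inference needs the literal reading of linear, and the misdescribed role of cross-validation adds nothing to it. Even then, squared error on a 0/1 outcome is the Brier score, a rescaled form of which the plan itself uses for overall accuracy.
- **That predictors will go in unstandardised.** The article states the intention to centre and normalise. What is wrong is the procedure named for it.
- **That the model would give risks outside 0 to 1, or rest on linear-LASSO coefficients.** The plan uses LASSO only to choose predictors and then refits by logistic regression, so penalised linear fits are never reported or used.

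The defence is also right that a count of differing sets overstates the harm. At a true AUC of 0.70, reshuffling the folds of a logistic LASSO changed the set more often than switching family did. At 0.80, switching family mattered more than fold noise (80% against 53%, and 70% against 33% with three repeats), so the effect on membership is not only noise.

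**Conclusion.** Wrong as written, and worth correcting as a matter of consistency in the stated analysis. The model named for the LASSO step contradicts the binary outcome and the final logistic model, and cross-validation is given a task that it cannot perform. These are statements in the methods text, not details left to a fuller document.

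The consequence is limited. If linear is followed literally, selection runs under a mismatched working model, and the predictor set often changes, by about one predictor on average in these simulations (0.5 to 1.3). The logistic refit confines the effect to set membership, and the effect on AUC is probably small. The sizes rest on assumed effects and on fewer cross-validation repeats than planned. Calibration and net benefit were not examined. The textual inconsistency itself rests on no assumption.

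**What to change.** Amend the paragraph under Development of the prediction model in three respects:

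1. Replace the linear model by LASSO-penalised logistic (binomial) regression.
2. State that predictors are standardised as a separate step before penalisation, with means and standard deviations computed within each training fold during cross-validation. Remove the statement that cross-validation does this.
3. State that the 10 repeats of 10-fold cross-validation serve to choose lambda, and name the criterion and rule, for example the lambda that minimises mean binomial deviance over the repeats. Other reasonable criteria exist; the point is to fix one before selection is run.

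The cost is two or three sentences and one software setting for the family. No new data are needed, and the development sample of 657 is unaffected.

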#### Preoperative potential predictors

A total of 15 preoperative potential predictors:

Demographic data including age, gender and body mass index.ASA physical status.Comorbidities including hypertension, diabetes mellitus and the age-adjusted Charlson Comorbidity Index score.Autonomic nervous system function (assessed by symptoms and anamneses).^26 27^Myocardial injury (assessed by anamneses and preoperative examinations).Vital signs in the surgical ward including MAP and HR.Preoperative anxiety assessed by the first four items of the Amsterdam Preoperative Anxiety and Information Scale (APAIS).^28^Preoperative frailty evaluated with the FRAIL (fatigue, resistance, ambulation, illnesses, and loss of weight) scale.^29 30^Preoperative volume of fluid infusion and fasting duration.

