#### Intraoperative potential predictors

A total of eight intraoperative potential predictors:

Vital signs including MAP and HR immediately before anaesthesia induction.Dose of anaesthetics used for induction, including propofol, etomidate, ciprofol, esketamine, fentanyl and sufentanil.

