#### Validation of the prediction model

The internal validation of the model will be performed using a bootstrapping method in the development cohort (n=657). A total of 500 samples will be generated and drawn randomly with replacement, and each sample will include the same number of patients in the development cohort. Moreover, the temporal validation will be conducted in the temporal validation cohort (n=281). The discrimination capability of the model will be assessed using the area under the receiver operating characteristic curve. Calibration of the model will be assessed using the Hosmer-Lemeshow goodness-of-fit statistic. The max-rescaled Brier score will be used to test the overall accuracy of the model. The clinical utility of the prediction model will be assessed using the decision curve analysis, and the results will be illustrated in a nomogram. Moreover, we will develop a web-based risk calculator by the shiny package to provide practical guide for clinic.

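### Refitting a plain logistic model on the LASSO-selected predictors discards the shrinkage, so the nomogram and web calculator are expected to give risks that are too extreme

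*Protocol article*

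**What the plan says.** Under *Development of the prediction model*, the article says "The development cohort (n=657) will be used to construct the model". LASSO is introduced there for two purposes, shrinking coefficients and selecting variables. Its penalty is tuned by 10-fold cross-validation repeated 10 times, and a best lambda is chosen. The section does not say whether that is the value with minimum cross-validated error (lambda.min) or the one-standard-error value (lambda.1se). The last step is: "Based on the optimal predictors derived from the LASSO analysis, we will use the multivariable logistic regression analysis to develop a prediction model". No penalty or shrinkage factor is stated for this final model. The Discussion likewise describes the output of LASSO as a set of predictors.

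Under *Validation of the prediction model*, "A total of 500 samples will be generated and drawn randomly with replacement", each of the size of the development cohort. Performance is then judged by AUC, the Hosmer-Lemeshow statistic, the max-rescaled Brier score and decision curves, and a temporal cohort of 281 follows. The products are a nomogram and a web calculator for clinical use. Under *Sample size estimation*, "we plan to recruit 657 patients for model development and internal validation (657=23×10/0.35").

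**The concern.** LASSO improves prediction in new patients partly by pulling coefficients towards zero. If only the variable list is kept and those variables are refitted by maximum likelihood in the same patients, the pull is removed. The coefficients are also estimated in the data that selected them, so they tend to be too large.

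Both products report an individual absolute risk. Coefficients that are too large overstate risk in high-risk patients and understate it in low-risk patients. AUC hardly registers this, because the ranking of patients changes little. Decision curves depend on the risks being calibrated, so they are affected too.

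**Working it through.** **Inputs from the article.** "A total of 15 preoperative potential predictors" and "A total of eight intraoperative potential predictors", so 15 + 8 = 23 candidates; "Considering a required number of 10 events per variable"; "the incidence of PIH was approximately 35% for patients undergoing elective non-cardiac surgery"; 657 development patients and 281 validation patients.

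**The plan's own figure.** 23 × 10 / 0.35 = 657.1, which reproduces 657. Expected events are 657 × 0.35 ≈ 230 in development and 281 × 0.35 ≈ 98 in temporal validation.

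**Is shrinkage needed at this size?** The heuristic shrinkage factor is S = 1 − p/LR, with LR = −n ln(1 − R²) and R² on the Cox-Snell scale. At 35% incidence the largest possible Cox-Snell R² is 1 − exp{2(0.35 ln 0.35 + 0.65 ln 0.65)} = 0.726. Take an assumed Nagelkerke R² of 0.20: R² = 0.20 × 0.726 = 0.145, LR = −657 ln(1 − 0.145) ≈ 103.1, and S = 1 − 23/103.1 = 0.78. At Nagelkerke R² of 0.10, 0.15, 0.30 and 0.40, S is 0.54, 0.70, 0.86 and 0.90. Only the strongest assumed signal comes near 0.90.

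**Simulation of the two-step procedure.** Settings: n = 657, 23 normal candidates with correlation 0.2^|i−j|, incidence 35%, LASSO logistic regression with 10-fold cross-validation (repeated twice rather than 10 times to save time), unpenalised refit on the selected predictors, calibration slope in 20,000 new patients, and 40 datasets per row. Sparse means five equal true predictors. Dense means all 23 contribute with declining weight. The signal strengths are assumptions. A slope below 1 means risks too extreme; above 1, too moderate.

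| Signal | True AUC | Refit, lambda.min | Refit, lambda.1se | LASSO coefficients, lambda.min | LASSO coefficients, lambda.1se | All 23, unpenalised |
|---|---|---|---|---|---|---|
| Sparse | 0.66 | 0.71 | 0.78 | 1.11 | 1.82 | 0.65 |
| Sparse | 0.73 | 0.85 | 0.94 | 1.22 | 1.77 | 0.81 |
| Sparse | 0.79 | 0.87 | 0.94 | 1.15 | 1.57 | 0.85 |
| Dense | 0.66 | 0.67 | 0.65 | 0.96 | 1.76 | 0.65 |
| Dense | 0.72 | 0.79 | 0.78 | 0.98 | 1.39 | 0.78 |
| Dense | 0.79 | 0.85 | 0.85 | 1.00 | 1.36 | 0.85 |

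The mean refit slope is below 1 in every row. At lambda.min, 57% to 100% of datasets fell below 0.90, and the refit was close to the unpenalised 23-predictor model, so most of the benefit of the penalty is gone.

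**Other settings.**
- Eight true predictors, correlation 0.3^|i−j|, true AUC 0.71 to 0.77: refit slopes 0.74, 0.78 and 0.84. Multiplying the refit by the bootstrap slope of the full procedure gave 0.94, 1.00 and 1.00.
- Eight true predictors, true AUC 0.73, 0.84 and 0.90: refit slopes 0.78, 0.85 and 0.89 at lambda.min, and 0.84, 0.91 and 0.94 at lambda.1se. In validation samples of 281, Hosmer-Lemeshow rejected the lambda.min refit in only about 27%.
- True AUC 0.68, 0.77 and 0.83: refit slopes 0.73, 0.85 and 0.87 at lambda.min, and 0.77 to 0.93 at lambda.1se.

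**What a slope means for a patient.** Suppose predictions are right at 35% (logit −0.619), so that true logit = −0.619 + slope × (predicted logit + 0.619). A displayed 80% (logit 1.386) is then really 66% at slope 0.65, 71% at 0.75 and 78% at 0.94. A displayed 10% (logit −2.197) is really 16%, 14% and 11%.

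**The case against.** Selecting by LASSO and refitting is a recognised two-step method and contradicts nothing else in the article. Shrinking the refit barely moves AUC (at most +0.003 in the simulations). Internal and temporal validation are both planned, and the article itself calls for multicentre validation. The signal may be strong, because the outcome is partly defined by baseline MAP, and ward MAP, pre-induction MAP and induction doses are all candidates. With a stronger sparse signal and lambda.1se the slope is about 0.94, a small effect. All of this stands, and it limits both the size and the grade of the point.

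It is also fair that the article never uses the word unpenalised, and that it does not say how the bootstrap results will be used. A reader might infer that the plan rules out any later shrinkage. The text does not support that: it is silent, and a condensed article may leave the use of the bootstrap to an analysis plan. The point therefore rests on the stated two-step procedure, not on that silence.

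A reader might also expect the temporal validation to expose the problem. That is not supported either. The only calibration measure named is Hosmer-Lemeshow in 281 patients, which would often miss it and which reports neither direction nor size.

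**Conclusion.** The point holds as an expectation. The stated method gives up the shrinkage that LASSO was brought in to provide, and with 23 candidates at 10 events per variable the displayed risks are expected to be too extreme. Mean calibration slopes in new patients ranged from about 0.65 to 0.94 across the simulations, lowest with weak signal.

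The direction did not change in any scenario. The size rests on assumptions that the article does not settle: signal strength (no expected AUC or R² is given), the lambda rule, an unpenalised final model, and a logistic LASSO (the section speaks of a linear regression model at that step). A reader might infer that the calculator is certain to be badly miscalibrated. With those inputs open, the documents do not support that. The grade is should-fix: a cheap improvement to a stated method, not an error that invalidates the study.

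**What to change.** Before building the nomogram and calculator, do one of the following.

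1. **Preferred.** Keep the refit. In each of the 500 bootstrap samples, repeat the whole procedure (cross-validated LASSO, then refit), apply the resulting model to the original 657 patients and record the calibration slope. Multiply the refitted coefficients by the mean of these slopes and re-estimate the intercept.
2. **Alternative.** Use the LASSO logistic coefficients at a prespecified lambda.min. Do not use lambda.1se, which over-shrinks (slopes of about 1.4 to 1.8). Even at lambda.min the LASSO coefficients can be somewhat too moderate when the signal is sparse (1.11 to 1.22 in the table), which is why the first option is preferred.

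Carry the chosen model unchanged into the temporal validation, and report its calibration slope and intercept there.

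The cost is a few lines of R, a sentence or two in the analysis section and slightly more computing. No new patients or data are needed. The reported odds ratios become less extreme and lose conventional p-values.
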